## Abstract

**Background:**

A psychoneurological symptom cluster composed of cancer-related fatigue, emotional distress, sleep difficulties, and pain is very common among patients with cancer. Cognitive difficulties are also frequently associated with this cluster. Network analyses allow for an in-depth understanding of the relationships between symptoms in a cluster. This paper details the study protocol of a longitudinal assessment of the psychoneurological symptom cluster in two distinct cohorts: breast cancer and digestive cancer survivors, using network analyses.

**Methods:**

Over two years, the symptoms involved in the psychoneurological symptom cluster, along with other common symptoms (e.g., digestive symptoms, financial difficulties) and variables (i.e., self-compassion, coping strategies) will be assessed in two cohorts: breast cancer survivors (*N* = 240) and digestive cancer survivors (*N* = 240). Online questionnaires will be completed at baseline, then 6, 12 and 24 months later. Network analyses will be used to assess the configuration of the symptom cluster at each measurement time and in each cohort. Comparison of networks between two measurement times or between the two cohorts will also be done with network comparison tests.

**Discussion:**

This study will enable a better understanding of the relationships between common symptoms endured by patients with cancer. The results will be employed to develop more cost-effective interventions which, ultimately, will significantly improve the quality of life of patients with breast or digestive cancer.

**Trial registration:**

ClinicalTrials.gov (NCT05867966). Registered on the 27th of April 2023. url: https://classic.clinicaltrials.gov/ct2/show/NCT05867966.

## Background

The presence of one psychoneurological symptom cluster (PNSC) composed of cancer-related fatigue (CRF), sleep difficulties, emotional distress, and pain is particularly well-documented among patients with cancer [1–3]. Cognitive impairments are also frequently associated with this symptom cluster [4, 5]. CRF is a distressing, persistent, and subjective feeling of physical, emotional and/or cognitive tiredness or exhaustion, which is related to cancer or its treatment. It is not proportional to the person’s recent activity and interferes with their routine functioning [6]. This multidimensional symptom is considered as the most severe one endured by patients with cancer, having a high impact on their quality of life (QOL) [7–9]. Yet, few attention has been received from the healthcare professionals [10]. Emotional distress (i.e., anxiety and depression), sleep difficulties (i.e., generally insomnia), pain, and cognitive difficulties (e.g., concentration or memory difficulties) are also very common among these patients and negatively influence their QOL [11]. In addition to their own negative consequences, these symptoms evolve together and reinforce each other, participating resulting in the high burden endured by patients with cancer [2, 12]. The mechanisms involved in the PNSC are uncertain [13, 14], but it is known that the more symptoms the patient presents, the lower their QOL [15]. Despite their severe impact and their persistence up to years after treatment completion, these symptoms remain underdiagnosed and undertreated [16]. The configuration of the PNSC (e.g., intensity of the relationships between different symptoms, core/central symptom of the cluster) seems to vary according to the cancer diagnosis [1, 2] and to evolve over time [17, 18]. Most studies in oncology focused on a single symptom, or on several symptoms considered independently from each other [3, 11, 19, 20]. However, the high prevalence of the PNSC underlines the relevance of studying multiple symptoms and their interactions.

Network analysis is an innovative method that underlines a deeper understanding of the connections between symptoms. By assessing and visualizing symptom clusters as dynamic systems of interacting symptoms, these analyses allow to study symptoms in their full complexity [1, 2, 12, 18] and to compare patterns of clustering between distinct populations [2, 21] or measurement times [1, 18]. Core symptoms within a network are the ones with the strongest associations with the other symptoms, which may play a critical role in activating them [22]. Thus, targeting them could allow to design more cost-effective interventions to impact the whole cluster [1–3, 11, 17, 18, 20, 23]. As network analyses in symptom studies are scarce, there is no consensus regarding the core symptom of the PNSC yet, as it seems to vary according to the population studied, the phase of the cancer trajectory, and the methodology used. Depression [1, 20], CRF [2, 15, 18], distress [3, 17], or anxiety [23] have been recurrently shown to be the core symptoms in studies on patients with cancer.

Cancer symptom management has often consisted in a “single symptom approach”, with the prescription of one specific intervention for each symptom reported by the patient, leading to complicated self-management of symptoms [11]. In the context of symptom clusters, interventions with benefits on one than more symptoms are thus highly relevant. Approaches such as mind-body techniques [11, 24–27], self-compassion learning [26–30], and cognitive-behavioural therapy [11] are relevant components to be included in such interventions. Different studies [10, 31–34] also suggested that the common-sense model of self-regulation of health and illness of Leventhal [31] (Fig. 1) could serve as a basis for developing interventions for cancer survivors, by targeting dysfunctional representations (top-down strategy) and enhancing adaptive coping (bottom-up strategy).

**Fig. 1 Fig1:**
[figure not shown]
Leventhal’s common sense model of self-regulation of health, adapted from [31]

The studies discussed above however suffer from several limitations. First, literature on symptom clusters in oncology is heterogeneous, due to the different statistical procedures used, cancer diagnosis included, symptoms considered, and time since diagnosis. Most of them have been conducted during or shortly after treatment (i.e., generally up to one year), whereas symptoms can develop lately and persist for years after treatment [16]. Second, most of them were cross-sectional and lacked of a longitudinal evaluation of the symptom clusters [20]. Thus, there is a need for rigorous studies investigating the presence and evolution of the PNSC among distinct populations of cancer survivors [35]. There is also a critical need for cost-effective personalized interventions to alleviate these symptoms [18, 35]. Targeting a core symptom, determined for a specific population, to impact the whole PNSC seems to be of particular interest in oncology, and responds to the need for more personalized care.

## Objectives

This study will consist of a longitudinal observational study that will assess the evolution of the PNSC (i.e., CRF, emotional distress, pain, sleep difficulties) in two cohorts of patients who had cancer (women with breast cancer and patients with digestive cancer), over two years, through network analyses. Evolution of other common symptoms (e.g., cognitive difficulties, nausea/vomiting, appetite loss), QOL, coping strategies, and self-compassion will be assessed in parallel. To note, the results from this study, especially the core symptom determined in each cohort, will be used in a future study to develop a new mind-body group intervention based on the common-sense model of self-regulation of health developed by Leventhal [31]. A randomized-controlled pilot trial will then be conducted to assess its feasibility and first benefits to improve the PNSC.

## Methods

### Design and procedures

We designed a longitudinal observational study to assess the evolution of the PNSC and the respective relevant variables in two distinct cohorts of cancer survivors (breast cancer survivors and digestive cancer survivors). Questionnaires (in French; see “Statistical analyses”for more details) will be completed online (on www.alchemer.eu) at four different times: at inclusion (T1), then 6 (T2), 12 (T3) and 24 (T4) months later. Written informed consent will be obtained from each participant at the beginning of the study (included at the beginning of the online questionnaires), and the inclusion criteria are checked at the beginning of the questionnaires, so that only participants who meet the criteria will be eligible to complete them. Participants will also have the possibility to contact the principal investigators by email or phone if needed (e.g., question, adverse event, or difficulty related to the study). At each measurement time, the risk of missing responses is very low, as the online questionnaires are designed in a way that does not allow for missing answers. The short duration of the questionnaires (approximately 20 min) will also increase completion and retention. All data will be anonymized: a code will be attributed to each participant and used during the entire study. Only the principal investigators involved in this study will have access to the complete datasets. Review of the trial process and difficulties encountered are discussed regularly between the researchers involved. As no standard procedure to determine the ideal sample size for network analysis is commonly used, the number of participants required in this study will be based on other studies in oncology using similar methodology [1–3, 17, 18, 20] and including between 172 and 342 patients per cohort, and set to 200. Accounting for a drop-out rate of 10% at one year in an observational study [36], and likely a higher drop-out rate at two years, we aim to include 240 participants in each cohort.

### Eligibility

Inclusion criteria will be: ≥18-years-old, fluent in French, diagnosis of non-metastatic breast cancer or digestive cancer (i.e., anal, colorectal, gastric, oesophageal, liver, pancreatic cancers), no history of cancer and not currently in relapse, time since end of active treatments (i.e., surgery, chemotherapy, radiation therapy) < 5 years (based on the methodology and recommendations of previous studies on symptom clusters in oncology [2, 3, 35, 37]). Breast and digestive cancer were chosen because they are among the most common cancers [38]. Thus, they would be easier to recruit, and our results could be of interest for more patients, as well as their relatives and healthcare professionals. Metastatic cancers will not be included, as done in one of our previous studies [26], in order to minimize the baseline differences in the sample, as the changing nature and complexity of metastatic cancers could make it difficult to compare the results with non-metastatic cases [39].

### Recruitment

Participants will be recruited over a 2-year period. Online questionnaires will be promoted and diffused through different means: websites of the involved departments and institutions, social networks, waiting rooms of the hospital, patients’ associations, and direct contact with health professionals working with these patients, in French-speaking Belgium but also in France or other French-speaking areas.

### Assessments

Approximate duration of questionnaires completion is 20 min at each measurement time. First, socio-demographic and medical data will be collected (i.e., sex, age, marital situation, education level, professional activity, cancer diagnosis, cancer stage, personal history of cancer and treatments, possible recurrence during the study, comorbidities, neurological and psychiatric history, history of drug or alcohol abuse, previous participation in a mind-body intervention, psychotherapy, major life events). Symptoms involved in the PNSC, as well as other common symptoms and QOL, will be assessed as follows:

*European Organization for Research and Treatment of Cancer - Quality of Life Core Questionnaire-30 (EORTC QLQ-C30)* [40]: This questionnaire (30 items) assesses the QOL of patients with cancer through 5 functional scales (physical, role, emotional, cognitive, and social functioning), three symptom scales (fatigue, nausea and vomiting, pain), a global health status/QOL scale and several single items for additional difficulties (dyspnoea, insomnia, appetite loss, constipation, diarrhoea, financial difficulties). Each item is scored on a 4-point Likert scale (‘not at all’ to ‘very much’), excepted for the global health status/QOL that is a 7-point scale (‘very bad’ to ‘excellent’). For functional scales and QOL scale, higher scores indicate better functionality and QOL. For symptom scales and single items, higher scores indicate higher symptomatology.*Multidimensional Fatigue Inventory (MFI-20)* [41]: This 20-item scale is designed to measure fatigue on 5 dimensions: general fatigue, physical fatigue, mental fatigue, reduced motivation and reduced activity. Suggested cut-off scores for significant general fatigue have been proposed for the general population: ≥ 11 (for men between 40 and 59 years-old), ≥ 12 (for women between 40 and 59 years-old), and ≥ 14 (for men and women older than 60 years-old) [42, 43].*Hospital Anxiety and Depression Scale (HADS)* [44]: This 14-item scale measures anxiety and depression, and has been validated for people with somatic illnesses. Scores between 8 and 10 on a dimension suggest the presence of anxious and/or depressive disorders, while scores between, 11 and 21 indicate the presence of such disorders.

Other variables of interest (i.e., coping strategies and self-compassion) will be assessed as follows:

*Ways of Coping Checklist* [45, 46]: This 27-item scale assesses coping through 3 dimensions: problem-oriented coping (score range: 10–40), emotion-oriented coping (score range: 9–36), and seeking social support (score range: 8–32). Higher scores indicate higher use of specific coping strategies.*Self-compassion scale* [47]: This 26-item questionnaire measures 6 dimensions related to self-compassion: self-kindness, self-judgment, common humanity, isolation, mindfulness, and over-identification, with higher scores indicating higher self-compassion. A total mean score is also generated and indicates low (i.e., score between 1 and 2.49), moderate (i.e., score between 2.5 and 3.49), or high (i.e., score between 3.5 and 5) self-compassion.

### Statistical analyses

Normality of data will be checked using Shapiro-Wilk test. Sociodemographic and medical data will be described using frequencies and percentages, means and standard deviations, or medians and interquartile ranges, depending on the distribution. To estimate the networks’ structure, a standardized score (z score [1]) will be calculated for each variable or dimension. Three centrality indices will be used: strength (number and strength of the direct connections to a node/symptom, i.e., sum of absolute weights; a high strength means that the symptom is more likely to occur in conjunction with other symptoms), closeness (node’s relationship to all other nodes; closer nodes mean stronger correlation), and betweenness (importance of a node in the average pathway between other pairs of nodes; a node with a higher betweenness has greater influence in the network) [1, 2]. Symptom networks will be created for both cohorts, at each of the four measurement times. To assess the differences between two networks (i.e., between breast and digestive cancers), and over time for each cohort (i.e., between T1, T2, T3 and T4), network comparison tests will be used [1, 17]. The evolution of the other variables over time (i.e., self-compassion, self-care agency, self-care strategies already implemented to manage CRF, and the representations about CRF) will also be measured and compared through repeated measures MANOVA and post-hoc comparisons.

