## Discussion

Recent studies highlighted the prevalence and negative consequences of the PNSC in oncology [1–3]. The core symptom of this cluster could be of major importance in the management of the cluster of symptoms as a whole [22] but it is still unclear which symptom from the cluster is the most central among patients with breast or digestive cancer. Determining this core symptom could allow to develop more cost-effective interventions, as addressing this symptom will likely decrease the other symptoms from the cluster [1–3, 11, 17, 18, 20, 23]. The development of multi-component interventions, especially those aiming to manage the whole PNSC, is then urgently needed in oncology [11]. We thus designed a longitudinal study assessing the PNSC and other symptoms in breast cancer and digestive cancer survivors, over 2 years. We hypothesize that: (1) one dimension of CRF or of emotional distress (i.e., depression or anxiety) will be the core symptom in all the obtained networks (i.e., for both cohorts and at each of the four measurement times), (2) the physical and mental dimensions of CRF will have different relationships with the other symptoms of the networks (e.g., physical fatigue could have stronger relationships with other physical symptoms such as loss of appetite or nausea/vomiting), (3) the configuration of the networks will differ according to the cohort considered (e.g., nausea/vomiting and diarrhoea/constipation could have stronger relationships with CRF, anxiety or depression in the digestive cancer cohort), and the measurement time (e.g., some correlations could weaken over time, as the intensity of some symptoms will decrease and became less important in the networks), and (4) self-compassion and coping strategies will not significantly evolve over time, even if a trend in this sense is possible due to a better adaptation to cancer.

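### Strength sums absolute edge weights but is read as co-occurrence, and no stated index for naming the core symptom uses edge sign

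*Protocol article*

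**What the plan says.** Statistical analyses names three centrality indices: strength, closeness and betweenness. Strength is described as the "sum of absolute weights; a high strength means that the symptom is more likely to occur in conjunction with other symptoms". Closeness and betweenness are described through how near nodes lie to each other and the paths between them, again without reference to sign. The only pre-processing named is that "a standardized score (z score [1]) will be calculated for each variable or dimension". On what is built, the section says: "Symptom networks will be created for both cohorts, at each of the four measurement times". The nodes are not listed.

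The core symptom is defined in the Background as the one most strongly associated with the other symptoms, which may play a part in activating them. Under Objectives, the core symptom found in each cohort is to feed the development of a later intervention. The Discussion gives the reason: "addressing this symptom will likely decrease the other symptoms from the cluster".

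On scoring direction, Assessments says of the QLQ-C30: "For functional scales and QOL scale, higher scores indicate better functionality and QOL", and then: "For symptom scales and single items, higher scores indicate higher symptomatology".

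**The concern.** The definition of strength and its interpretation do not match. A sum of absolute weights measures how tightly a node is connected, whatever the sign of the connections. Occurring together with other symptoms is a statement about positive connections only. If two symptoms are inversely linked given the rest (more of one goes with less of the other), that link adds to strength and is then read as co-occurrence, which is the reverse of what it shows.

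This matters because of what the index is for. The argument for targeting the core symptom is that it may activate the others and that reducing it should reduce them. That holds along positive edges. Along a truly inverse edge the expected direction is opposite. Nothing in the stated set of indices checks which kind of edge a highly ranked node owes its rank to.

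**Working it through.** The article states no edge weights or centrality values, so there is no figure to reproduce. All edge values below are assumptions.

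**1. How far the two indices can differ.** For node i with edge weights w_ij:
- strength = sum of |w_ij|
- signed sum (one-step expected influence) = sum of w_ij
- difference = 2 × (sum of |w_ij| over the negative edges)

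The difference is zero if no edge is negative.

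**2. Illustration, all nodes coded so that higher is worse.**
- Node A, edges +0.30, +0.20, -0.25: strength 0.30 + 0.20 + 0.25 = 0.75; signed sum 0.30 + 0.20 - 0.25 = 0.25. Difference 0.50 = 2 × 0.25.
- Node B, edges +0.25, +0.20, +0.20: 0.65 on both indices.

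Strength puts A ahead by 0.75 - 0.65 = 0.10. The signed sum puts B ahead by 0.65 - 0.25 = 0.40.

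**3. Range.** Let A's third edge be -x. Its strength is 0.50 + x and its signed sum 0.50 - x. The signed sum always ranks A below B. Strength ranks A above B only when 0.50 + x > 0.65, that is x > 0.15. Below that, both indices rank B first. So a disagreement in rank needs a negative edge of some size, not merely one that exists.

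**4. Does scoring direction change strength?** Reversing variable j multiplies row and column j of the correlation and partial-correlation matrices by -1. Every |w_ij| is unchanged, so strength is unchanged. This was checked on simulated data (8 assumed nodes, n = 200, z-scored) with the cognitive node reversed as 100 minus score:
- Largest change in any node's strength: about 1e-15 for a partial-correlation network and 7e-16 for an L1-penalised one (penalty 0.1).
- Largest change in closeness on distances 1/|w|: 2e-17. Betweenness on the same distances follows by the same argument; it was not computed.
- The reversed node kept strength 0.509, while its signed sum went from +0.39 to -0.39.

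Direction is therefore irrelevant to strength but decisive for a signed index and for reading the sign of an edge.

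**5. A node whose links are truly inverse.** In the assumed network, a protective node had edges -0.25, -0.30, -0.20, -0.15 and -0.05. Its strength is 0.95, just behind the top two symptoms (1.02 and 0.97), and its signed sum is -0.95. Read through the article's sentence, it would be nearly as co-occurring as the leading symptoms, although every one of its links is inverse.

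**The case against.** A reader might infer that the functional scales enter the network unreversed and that this distorts strength, so that the wrong node is named. The documents do not support either step. The article gives no node list and no coding direction, and a condensed article may leave both to the full protocol or analysis plan. And as shown above, reversal leaves strength and its ranks unchanged. A negative edge between cognitive functioning and fatigue that arises only from scoring is real co-occurrence of cognitive difficulty and fatigue, and strength counts it correctly.

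A reader might also infer that a wrong target will in fact be chosen. That is not shown.
- The article speaks of symptom networks. Self-compassion ("with higher scores indicating higher self-compassion"), a likely inverse node, is placed among the other variables analysed by repeated measures MANOVA.
- Constipation and diarrhoea, a plausible inverse pair, are both measured, and the third hypothesis in the Discussion puts them in the networks. But they lie outside the psychoneurological cluster as defined under Objectives, and the first hypothesis expects the core symptom to be a dimension of fatigue or distress. Whether their edge is negative is unknown before data.

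There is a fair case for absolute strength too. The Background definition of a core symptom has no sign condition, and strength is one of three indices, not the declared sole selector. In a signed sum, strong positive and negative links cancel: node A, with the higher strength of 0.75, falls to 0.25 and could be overlooked.

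What stands is the mismatch in the article's own sentence, and the lack of any stated index that uses sign when the rationale for the target depends on it.

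**Conclusion.** The point holds in a limited form and is minor. The co-occurrence reading of strength is wrong for any edge that remains negative once all symptom nodes point the same way, and no index described in the article would reveal this. The effect on a node is exactly twice the total of its negative weights. It is zero if there are none, and whether it changes the ranking depends on edge sizes that the article does not give. The illustrations rest on assumed weights and show what can happen, not what will. Opposite scale directions are not the cause; they matter only for interpreting edge signs and for computing a signed index.

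**What to change.** In Statistical analyses:
1. State that every symptom node is coded so that higher means worse before standardising, for example 100 minus score for any QLQ-C30 functional scale used as a node.
2. Add one-step expected influence, the signed sum of edge weights, as the index for naming the core symptom.
3. Keep absolute strength and report it beside the signed index, and limit the co-occurrence wording to positive edges.

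The first two belong together, because a signed sum is meaningful only after alignment. Fixing the rule before the networks are seen also avoids choosing the index afterwards.

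The cost is a few lines of analysis text and no new data. There are two drawbacks: positive and negative links can cancel in the signed sum, and comparison with earlier studies that reported only strength is slightly less direct. Reporting both indices meets both drawbacks. If all aligned edges turn out positive, the two give the same answer.

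### The single-wave symptom networks show association without direction, yet the core symptom they yield is read as a driver and used as the target of the next intervention

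*Protocol article*

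**What the plan says.** All references are to the protocol article.

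- **Data.** Under Design and procedures, questionnaires are completed "at four different times: at inclusion (T1), then 6 (T2), 12 (T3) and 24 (T4) months later".
- **Networks.** Under Statistical analyses, "Symptom networks will be created for both cohorts, at each of the four measurement times". With two cohorts and four waves that is 2 × 4 = 8 separate networks.
- **Indices.** Strength is a "sum of absolute weights; a high strength means that the symptom is more likely to occur in conjunction with other symptoms". For closeness, "closer nodes mean stronger correlation". For betweenness, "a node with a higher betweenness has greater influence in the network".
- **Use of time.** Differences are tested between cohorts and "over time for each cohort (i.e., between T1, T2, T3 and T4), network comparison tests will be used". The repeated measures MANOVA is reserved for the other variables, such as self-compassion, and not for the symptoms.
- **Use of the result.** The Background describes core symptoms as the most strongly associated ones and adds that they may activate the rest. The Discussion says that "addressing this symptom will likely decrease the other symptoms from the cluster". The Objectives say that "the core symptom determined in each cohort, will be used in a future study to develop a new mind-body group intervention", and the last paragraph of the Discussion repeats that the intervention will target the core symptom of each cohort.
- **Limitations.** Those listed are sample size, the five-year window and the restriction to two populations. Direction is not among them.

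**The concern.** Saying that treating a symptom will reduce the others is a statement about direction. The indices that select the symptom carry none: a sum of absolute weights is the same whether the symptom acts on its neighbours or is acted on by them. A symptom that merely collects the effects of the others can therefore come out as core, although changing it would change nothing else.

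At stake is the choice of target for the next intervention and its pilot trial. Larger samples or better estimation of the same networks would not cure this. The same participants are followed over four waves, so evidence on temporal order is available, but none of the stated analyses uses it for the symptoms. Network comparison tests ask whether two finished networks differ, not which symptom comes first.

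**Working it through.** **The plan's own figure.** The article gives no number for this point. The sample size enters only as an input: 200 per cohort, set by precedent. Inflating for the stated 10% drop-out gives 200/(1 − 0.10) = 223. The planned 240 corresponds to 1 − 200/240 = 16.7%, which fits the remark that two-year drop-out is likely higher. Nothing here is wrong, and the point does not depend on it.

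**Step 1: symmetry.** I take edges to be partial correlations. This is an assumption, because the article names no estimator. With V the covariance matrix and P its inverse, the edge is r_ij = −P_ij/√(P_ii P_jj), and strength is s_i = Σ_j |r_ij| over j ≠ i. Since r_ij = r_ji, strength cannot separate effects out of a symptom from effects into it.

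**Step 2: an exact example.** Take four symptoms.
- Model 1: symptom 0 causes 1, 2 and 3, each with correlation 0.5.
- Model 2: symptom 1 causes 0, and 0 causes 2 and 3, each with correlation 0.5.

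Both give 0.5 between symptom 0 and each other symptom, and 0.5 × 0.5 = 0.25 among the others. The correlation matrices are identical, and so are the networks: strength 1.225 for symptom 0 and 0.408 for each other. Yet changing symptom 0 alters three symptoms under model 1 and only two under model 2.

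**Step 3: lag-1 illustrations.** All coefficients are assumptions. With lag matrix B and unit innovations, V solves V = B V Bᵀ + I. Samples have n = 200. Out-prediction is the sum of a symptom's standardised lagged coefficients on the other symptoms, by least squares on two waves.

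- Six symptoms: autoregression 0.5, focal cross-lags 0.2.
- Eight symptoms: autoregression 0.5, background cross-lags 0.03, focal cross-lags 0.15.

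| Focal symptom | Strength, focal v each other | First on strength | First on out-prediction |
|---|---|---|---|
| 6 symptoms, driver | 0.49 v 0.32 | 48% | 100% |
| 6 symptoms, consequence | 0.57 v 0.17 | 80% | 3% |
| 8 symptoms, consequence | 0.92 v 0.30 | 93% | 1 to 3% |
| 8 symptoms, driver with no input | 0.42 v 0.51 | 5% | almost 100% |
| 8 symptoms, driver with 0.03 input | 0.66 v 0.57 | 24% | almost 100% |

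The last two rows differ only in whether the driver receives the small background input. That alone reverses the order of the strengths.

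**Step 4: sensitivity.**
- Over 54 settings (6, 8 or 12 symptoms; focal effect 0.10 to 0.20; background 0 or 0.03; same-wave noise correlation 0 to 0.4), strength put the consequence symptom first in 9 to 100% of samples and the driver in 0 to 49%. Out-prediction favoured the driver in every setting, but in the weakest only by 16% to 14%.
- If effects act within a wave (assumed 0.3, cross-lags 0.03), strength names the driver in 93 to 100%. Lagged out-prediction then separates poorly: two codings of this assumption gave 72% (consequence) v 94% (driver), and 35% v 30%.

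**The case against.** **Scope.** Only a journal article is shown. It does not call the networks undirected, and a fuller plan could contain a temporal model. That is fair, and the absence of direction is inferred from the index definitions and from one network per wave. But the article states both its network analyses and the conclusion it expects from them, and these do not fit together. That is more than an omitted detail.

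**Fit to the aims.** The hypotheses concern the core symptom at each time, relations within networks, and differences between cohorts and times. Per-wave networks with comparison tests answer these. This stands: the descriptive aims are served. A reader might infer that the article contradicts itself by faulting earlier work as cross-sectional. It does not, since its complaint is the lack of longitudinal evaluation, and four compared waves provide one.

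**Hedging.** The causal wording is qualified, the intervention is multi-component and belongs to a future study, and a pilot trial would examine its first benefits. So calling the target the study's main product would go too far. The target is nonetheless said to follow from the core symptom.

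**Size.** A reader might infer from the 93% and 5% in the table that strength favours consequences and rejects drivers. The 5% needs a driver with no input at all. It becomes 24% with the background kept, 48% in the six-symptom system, and 93 to 100% when effects are fast.

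**The remedy.** Lagged models show precedence, not cause. With no cross-lagged effects but an assumed stable trait loading most on one symptom, two-wave regression still ranked that symptom first in about 70% of samples. The real networks may also be larger than those simulated: nine QLQ-C30 symptom scales or items, five MFI-20 dimensions and two HADS scales make 16, so the near-perfect lagged recovery is optimistic. These points stand, and they rule out out-prediction as the sole rule for the target.

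**Conclusion.** The concern holds as a mismatch between analysis and inference. The stated single-wave networks and centrality indices cannot distinguish a driver from a consequence, while the Background, Objectives and Discussion treat the core symptom as one whose treatment should lower the others.

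The robust part is the symmetry, which needs no lag assumption; it rests on reading the networks as undirected. The percentages rest wholly on assumed coefficients. A pure consequence is ranked first in about 80 to 99% of samples in the main settings, and less often when effects are weak. A driver is ranked first in anywhere from 0 to 100%.

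It does not follow that the core symptom found here will be a consequence, only that the planned analysis could not tell. Nor does it follow that a lagged network would settle the matter.

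**What to change.** - Alongside the per-wave networks, pre-specify a regularised cross-lagged panel network per cohort, with each symptom regressed on all symptoms at an earlier wave. Allow for the spacing: T1 to T2 and T2 to T3 span 6 months, T3 to T4 spans 12. State in advance how the lagged networks will be read together if they differ.
- Report in- and out-prediction next to strength, as supporting evidence for the target and not as the only rule.
- State that lagged estimates show temporal precedence and not causation, and may miss effects faster than 6 to 12 months.
- Where the lagged results do not support the cross-sectional core symptom, report it as the most strongly associated symptom and do not claim that treating it will lower the others.
- Add the lack of direction to the limitations in the Discussion.

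**Cost.** Analysis time and some rewording; no new data. Lagged estimates use only participants with both waves, so they are less precise. For example, 240 × 0.90 = 216 per cohort would remain at one year under the stated drop-out, and fewer at two years, for which no rate is given.
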